#### Main outcome variables

The primary variable will be prolonged abstinence from smoking, and a secondary variable occasional abstinence (point prevalent abstinence), both of which will be validated using confirmation by coximetry at 12 months post-intervention. The cut-off point to confirm abstinence will be 10 ppm, since lower values indicate a non-smoker and higher values reflect having smoked within the preceding 12 to 24 h [34].

The criterion to establish abstinence takes into account the Society for Research on Nicotine and Tobacco recommendations and definitions [35]:

- *Continuous abstinence *refers to sustained abstinence between the point of intervention and a follow-up point.

- *Prolonged abstinence *refers to sustained abstinence from an initial "grace period" until a follow-up point. The "grace period" is understood as the time immediately after a definite quit date or intervention during which continued smoking is not considered failure to quit. For most studies, the recommendation is that this period not exceed 2 to 4 weeks.

- *Point prevalence abstinence *refers to abstinence during a time window immediately before the follow-up point (usually 7 days).

- *Failure to quit *refers to a smoking relapse (of any type) lasting 7 consecutive days (defined by the U.S. National Heart, Lung, Blood Institute).

In general, continuous abstinence is accepted as the *gold standard*, but this is a very rigorous measure; therefore, prolonged abstinence is preferred because it allows inclusion in the analysis of subjects who achieve a sustained abstinence after a transitional "grace period" and whose effort would otherwise be considered failure.

#### Sample size calculation

To achieve the study's main objective, sample size is calculated in accordance with the following parameters: identification of a difference equal to or greater than 8% between the intervention group and control group with regard to abandonment or reduction of tobacco use, a 10% abandonment or reduction in the control group, an alpha risk of 0.05, and a beta risk of 0.20 in a two-tailed contrast. Consequently, for this study it will be necessary to randomize a total of 590 subjects (295 in each group). Taking into account a withdrawal rate of 10%, the total sample size will be 649 subjects.

At each of the 12 participating centres, it should be reasonable to expect the associated researchers to include about 50 participants in this study (25 in each group).

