At present, the use of spirometry as a motivational tool for smoking cessation continues to be a controversial topic. The most recent Cochrane review of the assessment of biomedical risks as a quit-smoking aid insists that, due to the scarcity of high-quality analyses, no definitive conclusions can be reached about the effectiveness of this approach [21]. However, it also points out that spirometry had a significant effect in the only high-quality study, published in 2008 by Parkes et al. [22]. This clinical trial included 561 smokers older than 35 years who, after spirometry testing, were randomized to study groups, one of which received a summary of the results, describing their "lung age" and comparing it with their chronological age. After 12 months follow-up, abstinence rates confirmed by urinary cotinine levels were significantly higher in the intervention group (13.6% vs 6.4%, *P *= 0.005) and these subjects had a higher probability of abandoning their habit than those who did not receive this explanation (RR: 2.12; IC95%: 1.24-3.62). Moreover, Kotz et al. published a clinical trial in 2009 with the hypothesis that early detection of COPD and the provision of information about the results could be more effective than standard efforts to help smokers to quit [23]. The study evaluated 296 smokers aged 35-70 years with COPD detected by spirometry testing, who were randomly assigned to either confrontational counselling for smoking cessation in which a nurse respiratory specialist provided feedback on the results (experimental group) or "care as usual" for smoking cessation delivered by the general practitioner. After 52 weeks of follow-up, the intervention group achieved higher abstinence rates (11.2% vs 5.9%), although without reaching statistical significance (OR: 2.02; IC95%: 0.63-6.46). These studies appear to present contradictory results, although congruence emerges if we analyze them in detail: the use of spirometry in "healthy" smokers increases motivation (and the probability of quitting smoking), while confrontation with their lung function data is less effective in subjects with COPD. More recently, in 2010, McClure et al. [24] published a clinical trial with 536 smokers, recruited from the general North American population, who were randomized to receive a brief motivational intervention for smoking cessation (≈20 min), including spirometric testing and feedback; no differences in abstinence rates were found at 1 year of follow-up. However, in a later publication they reported that the participants with changes in their lung function tests made greater use of quit-smoking services and achieved an abstinence rate almost double that of controls at 6 months (17.2% vs 8.9%, *P *= 0.05; OR: 2.13, IC95%: 1.04-4.5), although the effect was diluted at 12 months (16.2 vs 11.3, *P *= 0.26; OR: 1.52, IC95%: 0.73-3.1) [25]. Therefore, given these other results, they concluded that more research is NEEDED to determine whether the impact of spirometry feedback differs according to the deterioration in the smoker's pulmonary function.

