
## Objectives

The main objective of this study is to evaluate the effectiveness in the primary care setting of a structured motivational intervention and feedback on spirometry data to achieve smoking cessation, compared with usual clinical practice and assessed with respect to quit rates at 12 months after the intervention.

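### The 80% power is worked out for quitting or cutting down, not for the primary variable, so it is not shown to apply to CO-validated prolonged abstinence

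*Protocol article*

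**What the plan says.** Three sections of the protocol article bear on this.

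- **Sample size calculation.** The paragraph opens "To achieve the study's main objective, sample size is calculated in accordance with the following parameters". The effect is "identification of a difference equal to or greater than 8% between the intervention group and control group", and both the difference and the control rate are set "with regard to abandonment or reduction of tobacco use, a 10% abandonment or reduction in the control group". With two-sided alpha 0.05 and beta 0.20, this gives 295 per group (590 in total), raised to 649 for 10% withdrawal.
- **Objectives.** The main objective is "assessed with respect to quit rates at 12 months after the intervention".
- **Main outcome variables.** "The primary variable will be prolonged abstinence from smoking", with point prevalence abstinence as a secondary variable, "both of which will be validated using confirmation by coximetry at 12 months post-intervention". The cut-off is 10 ppm. Reduction in consumption is not listed as an outcome.

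The Analysis strategy section plans rates of continuous, prolonged and point prevalence abstinence. It uses consumption data to compare those who fail to quit with those who succeed. It describes no between-arm test of quitting or reducing combined.

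**The concern.** The sample size paragraph says that it serves the main objective, but its two inputs belong to a broader event than the one the objective and the primary variable name. The composite wording is attached both to the difference and to the control rate, and no threshold for reduction is given.

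Everyone with validated prolonged abstinence has also given up or reduced, but the reverse does not hold. The control rate for the primary variable therefore cannot exceed the composite's rate, and the difference between arms may be smaller or larger than 8 points. A null result on abstinence would be read against a stated 80% that the text ties to another event.

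**Working it through.** **Inputs.** From the Sample size calculation: 10% vs 18%, two-sided alpha 0.05, power 0.80, 295 per group. From the Background: 12-month (or 52-week) abstinence of 6.4% vs 13.6%, 5.9% vs 11.2% and 11.3% vs 16.2% (control vs intervention). Everything marked as an assumption below is not in the document. The 295 per group is taken as the number analysed, since the 649 is meant to allow for withdrawals.

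**Formula.** Two proportions, pooled variance under the null, no continuity correction, with p̄ = (p1 + p2)/2:

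n = [1.960·√(2p̄(1−p̄)) + 0.842·√(p1(1−p1) + p2(1−p2))]² / (p1−p2)²

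Power = Φ{ [|p1−p2|·√n − 1.960·√(2p̄(1−p̄))] / √(p1(1−p1) + p2(1−p2)) }

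**Step 1: reproduce the plan's figure.** For 10% vs 18%, p̄ = 0.14, √(2·0.14·0.86) = 0.4907 and √(0.10·0.90 + 0.18·0.82) = 0.4874.

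n = (0.9618 + 0.4102)² / 0.08² = 294.1, so 295 per group and 590 in total, which matches.

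Power at 295 = Φ[(0.08·17.176 − 0.9618)/0.4874] = Φ(0.846) = 80.1%.

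The calculation is correct for the composite.

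**Step 2: what passes from the composite to abstinence.** Write the composite as validated prolonged abstinence (A) plus everything else it contains (R: reduction, and quitting that is not prolonged or not confirmed). The plan fixes only the sums: A + R = 10% in the control arm, and ΔA + ΔR = 8 points. If R is equal in the two arms, ΔA is the full 8 points at a control rate below 10%, and power rises. If A and R grow in the same ratio, ΔA is below 8 points, and power falls. The plan does not say which it expects, so the direction is open.

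**Step 3: power for abstinence at 295 per group.**

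| Scenario | Control vs intervention | Power | n per group for 80% |
|---|---|---|---|
| Cited: smokers over 35, not described as selected for COPD | 6.4% vs 13.6% | 83% | 272 |
| Cited: smokers with COPD | 5.9% vs 11.2% | 63% | 436 |
| Cited: subgroup with lung function changes | 11.3% vs 16.2% | 41% | 775 |
| Assumption: ratio 18/10 = 1.8 kept at 5% control | 5% vs 9% | 48% | 638 |
| Assumption: 8 points kept at 5% control | 5% vs 13% | 93% | 200 |
| Assumption: 8 points kept at 6% control | 6% vs 14% | 90% | 220 |
| Assumption: 8 points kept at 7% control | 7% vs 15% | 88% | 239 |

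The COPD and lung-function-change rows describe people this trial does not randomise. Under Allocation of study groups, only subjects with normal spirometry are assigned. The 11.3% control rate also lies above the plan's own 10% for the wider composite, so that row cannot hold together with the plan's assumption.

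**Step 4: detectable difference.** Solving the power formula for 80% at 295 per group gives about 6.7 points at a 6% control rate (assumption) and about 8.0 points at 10%.

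**The case against.** The strongest reply is that the wording is loose and no more. The paragraph announces that it serves the main objective, which is quit rates. The cited control abstinence rates (5.9% to 11.3%) bracket 10%, so 10% and 18% may have been meant as abstinence rates. The nearest comparator gives 83%, close to the stated 80%. The 8-point target is only 0.8 above that comparator's 7.2 points (13.6 − 6.4), and choosing a target difference is a design judgement. The primary variable, its time point and its validation are clear. No planned test depends on the composite, and 95% confidence intervals are promised for all measures, so a null result can be judged from its interval.

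Most of this stands, and it limits the point to a correction of the sample size paragraph. It does not remove the mismatch: the text says quitting or reducing for both inputs, and no other section says that the two figures refer to abstinence.

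A reader might infer from the 63% and 41% rows that the trial is underpowered. The documents do not support that. Those rows come from groups that are not randomised here, and the Background itself reads the evidence as spirometry working better in healthy smokers than in those with COPD. Keeping the 8 points at a lower control rate raises power above 80%. Nor can one infer that a correct statement would necessarily be less favourable.

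**Conclusion.** The point holds as a mismatch of endpoint and should be fixed. The 295 per group and 80% power are correctly computed for a composite of quitting or reducing, while the objective and the primary variable concern abstinence alone. The stated 80% is therefore not shown to apply to the primary variable.

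The size and direction of the discrepancy are unknown. The plausible range is wide: 83% on the nearest cited evidence, and 48% to 93% under an assumed 5% control rate, depending on whether the ratio or the absolute difference is kept. These figures rest on 295 analysed per group, the uncorrected pooled test that reproduces the plan's own N, and the assumptions marked in the table.

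**What to change.** Keep N. Rewrite the paragraph with a control rate and a target difference for CO-validated prolonged abstinence at 12 months, justify both for smokers with normal spirometry, and restate what 295 per group delivers. For example: 80% power for a difference of about 6.7 points if control abstinence is 6% (assumption), or about 8.0 points if it is 10%. Rates from a COPD-only trial should not serve as the printed benchmark.

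If 10% and 18% were meant as prolonged-abstinence rates, say so, justify them and delete the words on reduction. N and power then stand. Deleting those words without such a justification would not be enough. If reduction in consumption is of interest, define it and list it as a secondary outcome.

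The cost is one reworded paragraph and no extra participants. The stated power may move in either direction.

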#### Analysis strategy

Data will be drawn from a centralized database and grouped so that those responsible for analysis will be blinded to participants' study group assignment.

The effectiveness of randomization to assess the comparability and consistency of intervention and control groups will be checked in terms of the similarity of the distribution of the variables of interest at baseline. Losses to follow-up in each group will be quantified and assessed to rule out a possible selection bias.

All analysis will be conducted on the principle of intention to treat. Losses to follow-up will be quantified in each group and assessed to determine whether any possible bias was introduced to the results. A "worst-case analysis" strategy will be used, assuming that the expected response occurred in the control group patients lost to follow-up and did not occur in the intervention group. Using this assumption, the data will be reanalyzed and the magnitude of the observed difference between the initial results and the "worst-case" estimates will be assessed. This approach is valid except in the unlikely case that losses to follow-up exceed 20%.

Standard statistical tests will be used for both quantitative and qualitative variables described (e.g. means, standard deviations, medians, proportions).

Continuous abstinence, prolonged abstinence rates, and point prevalence abstinence at 6 and 12 months after intervention will be calculated, along with Cox analysis of survival (abstinence). In cases of failure to quit, consumption data, motivation, and number of attempts to quit smoking during follow-up will be collected and compared with those who achieved a level of abstinence.

The results will be presented using both relative and absolute measures: relative risk (RR) and relative risk reduction (RRR) and absolute risk reduction (ARR) and the number needed to treat (NNT), or number of smokers who must try to quit to succeed in getting one to remain abstinent. All measures will be expressed with their respective confidence intervals (CI) of 95%.

To assess the influence of studied parameters on the rates of abstinence and failure, logistic regression will be used, calculating odds ratios (OR) and 95% CI. As part of the statistical analysis, multiple logistic regression models will be fitted to adjust for potential confounding covariates of the primary outcome (age, sex, educational level, number of previous quit attempts, nicotine dependence, motivation to quit smoking, comorbidity, etc.) [36,37].

Statistical analysis will be performed with SPSS version 14.0. The tests will be considered significant when *P *< 0.05.

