#### Follow-up period

All subjects will be evaluated during a telephone follow-up at 6 months post-intervention (visit 2) to determine whether there has been any change in their smoking status and to record new data about tobacco consumption or, where applicable, to record quit date. Finally, at 12 months after inclusion in the study, they will be scheduled for their final study visit (visit 3), which will take place at the corresponding centre. At this last visit, new data will be collected on each subject's smoking habit (current consumption, dependence, motivation and stage in the change process) or, where applicable, quit date. Patients who claim to have quit smoking will undergo a breath test to measure expired CO.

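### The worst-case rule scores every lost control as abstinent, with no exception for those whose 6-month record already establishes failure

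*Protocol article*

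**What the plan says.** All places are in the Methods of the protocol article.

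- **Analysis strategy.** Analysis is by intention to treat. For losses there is a worst-case reanalysis, "assuming that the expected response occurred in the control group patients lost to follow-up and did not occur in the intervention group". Its estimates are set beside the initial results, and the approach is called valid unless losses pass 20%. The rule depends on loss alone; a status already on record makes no difference. The same section plans continuous, prolonged and point prevalence abstinence rates at both 6 and 12 months.
- **Follow-up period.** An earlier contact is planned here: "All subjects will be evaluated during a telephone follow-up at 6 months post-intervention (visit 2) to determine whether there has been any change". Smoking status is recorded at that call, along with consumption or a quit date. Visit 3, at 12 months, is the last.
- **Main outcome variables.** The primary outcome is prolonged abstinence, which "refers to sustained abstinence from an initial 'grace period' until a follow-up point". The grace period may follow either a set quit date or the intervention, and an upper limit of 2 to 4 weeks is cited as the usual recommendation. Continuous abstinence must hold from the intervention itself. Failure is a relapse that lasts 7 days in a row. Point prevalence, a secondary outcome, looks only at a short window before the follow-up point.

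**The concern.** A worst-case bound should put the most unfavourable possible value where an outcome is unknown. It should not replace an outcome that collected data have already settled.

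Take a control who reports smoking at the 6-month call and is then lost. That person has failed 12-month continuous abstinence, whatever happens later. If the grace period runs from the intervention, and the smoking meets the 7-day failure criterion, the person has failed 12-month prolonged abstinence too. Under that reading the plan would count the same person as a failure in the 6-month prolonged rate and as a success in the 12-month worst-case rate.

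Only the control arm is distorted, because lost intervention participants are scored as failures anyway. The gap between the initial and worst-case results is what the plan will use to judge robustness. A real effect could look fragile because recorded failures had been overwritten.

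**Working it through.** **1. The plan's own figure.** The Sample size calculation section gives "a 10% abandonment or reduction in the control group", "identification of a difference equal to or greater than 8% between the intervention group and control group", and "an alpha risk of 0.05, and a beta risk of 0.20 in a two-tailed contrast". With p1 = 0.10, p2 = 0.18 and mean 0.14, the pooled formula without continuity correction is

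n = [1.960 × √(2 × 0.14 × 0.86) + 0.842 × √(0.10 × 0.90 + 0.18 × 0.82)]² / 0.08² ≈ 294.1, rounded up to 295 per group.

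This matches "randomize a total of 590 subjects (295 in each group"). The allowance for losses also reproduces: 590 × 1.10 = 649, as in "Taking into account a withdrawal rate of 10%, the total sample size will be 649 subjects". That is about 324.5 per arm, and at 10% loss about 32 lost controls.

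**2. Inputs for the check.**

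- Rates among those followed: 10% and 18%. The section states them for quitting or reducing; using them as abstinence rates is an assumption.
- Loss L, taken as equal in both arms: 10% (the planned allowance) and 20% (the limit in Analysis strategy).
- f: the share of lost controls whose 6-month record already establishes failure for the outcome in question. The documents do not give it, so the full range 0 to 1 is shown.

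**3. Formulas.**

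- Control, rule as written: (1 - L) × 0.10 + L
- Control, established failures kept as failures: (1 - L) × 0.10 + L × (1 - f)
- Intervention, either way: (1 - L) × 0.18
- Overstatement of control abstinence: the difference between the two control lines, L × f

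**4. Rule as written (f = 0).**

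- L = 10%: control 0.09 + 0.10 = 19.0%; intervention 16.2%; difference -2.8 points.
- L = 20%: control 0.08 + 0.20 = 28.0%; intervention 14.4%; difference -13.6 points.

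**5. Established failures kept as failures** (intervention minus control, in points; p from a pooled z-test with 324.5 per arm).

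| f | L = 10% | L = 20% |
|---|---|---|
| 0 | -2.8 (p = 0.35) | -13.6 (p < 0.001) |
| 0.25 | -0.3 (p = 0.92) | -8.6 (p = 0.005) |
| 0.50 | +2.2 (p = 0.43) | -3.6 (p = 0.21) |
| 0.75 | +4.7 (p = 0.08) | +1.4 (p = 0.60) |
| 0.90 | +6.2 (p = 0.02) | +4.4 (p = 0.09) |
| 1 | +7.2 (p = 0.006) | +6.4 (p = 0.010) |

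**6. One illustrative value.** Suppose 70% of lost controls were reached at 6 months and 90% of those had an established failure. Both figures are assumptions. Then f = 0.70 × 0.90 = 0.63, about 20 of the 32. At L = 10%, control = 0.09 + 0.10 × 0.37 = 12.7%, the difference is 16.2 - 12.7 = +3.5 points, and the overstatement is 6.3 points.

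**7. Where the sign changes.** The difference is zero at f = 1 - (1 - L) × 0.08 / L, which is 0.28 at 10% loss and 0.68 at 20% loss.

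**The case against.** The strongest reply is that a worst-case analysis is meant to be extreme, that it stands beside the main result without replacing it, and that no decision rule hangs on it. All of that is right, and it limits the point to how informative the bound is. It does not justify giving a value that recorded data exclude.

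A second reply is that the protocol does not define loss to follow-up, and that the full protocol or analysis plan may treat someone with a recorded failure as having a known outcome. If so, the point is met. The rule as published has no such limit.

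Two stronger readings are tempting, and the documents do not support them.

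- *The 6-month call shows that many lost controls were smoking.* No follow-up data exist in a protocol. Participants lost before the call will have no record, and nothing says how losses divide around it.
- *A smoker at 6 months cannot meet the primary outcome.* The grace period may start at a quit date, and quit dates are recorded at both later visits. On that reading someone who quits after the call could still qualify at 12 months. A slip shorter than 7 days may also fall short of the failure criterion. Only the conflict with continuous abstinence is unconditional. For 12-month point prevalence there is no conflict, because a later quit is possible.

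**Conclusion.** The point holds as a defect in a sensitivity analysis. The stated rule can count as abstinent a control whose failure is already on record. This is so for 12-month continuous abstinence under any reading. For the primary outcome it depends on a grace period counted from the intervention and on smoking that meets the failure criterion.

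The overstatement of control abstinence is L × f: 0 to 10 points at 10% loss and 0 to 20 points at 20% loss. Under the planning rates and equal losses, the bound at 10% loss lies anywhere from -2.8 to +7.2 points according to f, and changes sign once f exceeds 0.28. The figure of +3.5 points rests on the assumed f of 0.63.

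A reader might infer that the trial's main result is biased against the intervention, or might weigh the overstatement against the 8-point target. Neither follows: the rule acts only in the reanalysis, and the target was set for quitting or reducing, not for prolonged abstinence. The point is worth correcting before analysis, because the correction uses data the trial already plans to collect.

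**What to change.** 1. In Main outcome variables, state where the grace period starts for this trial.
2. In Analysis strategy, add that a participant whose visit 2 record already meets the failure definition for an outcome is a known failure for that outcome at 12 months, in both arms. For continuous abstinence, any recorded smoking since the intervention is enough. For prolonged abstinence, the recorded smoking must fall after the grace period and meet the protocol's 7-day failure criterion.
3. Limit the worst-case assumption to lost participants whose outcome is still undetermined.
4. Leave the existing rule in place for point prevalence at 12 months.

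The cost is a few sentences and no new data. The downside is that a mistaken report of smoking at 6 months could not be corrected later.

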### Setting and study sample

The study population will be recruited during consultations in 12 primary care practices in the province of Tarragona (Spain) managed by the Catalan Health Institute, 8 of which are urban and 4 rural, serving an adult population (aged > 18 years) of 195, 343 patients. Candidates for participation are smokers aged 35 to 70 years who visit a centre for any reason during regular office hours, and who meet all inclusion criteria and none of the exclusion criteria.

- *Inclusion criteria*: current smoker, with a cumulative consumption of more than 10 packs/year.

Current smoker is defined as having smoked daily during the past month, regardless of the quantity. Cumulative consumption is defined as the daily average of cigarettes smoked, multiplied by the number of years of smoking, divided by 20.

- *Exclusion criteria*:

1) Any evidence of previous diagnosis of a respiratory disease,

2) Functional pulmonary testing conducted within the previous 12 months,

3) Presence of any chronic or terminal condition that changes the baseline parameters or complicates the testing and analysis to be conducted during the study period,

4) Impossibility of completing follow-up for any reason,

5) Patient refusal to continue with the study.

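### The worst-case analysis of losses is declared valid up to 20%, but with the plan's own rates it cannot support the planned effect beyond about 2% loss and changes sign at 7.4%

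*Protocol article*

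**What the plan says.** The Analysis strategy section of the protocol article places all analyses under intention to treat and says that losses will be counted in each group. It then fixes one assumption for lost participants, "assuming that the expected response occurred in the control group patients lost to follow-up and did not occur in the intervention group". The data are reanalysed on that assumption, and the gap between the reanalysis and the initial results is assessed. The section closes the point with a validity claim: "This approach is valid except in the unlikely case that losses to follow-up exceed 20" per cent.

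The Sample size calculation section supplies the figures needed to test that claim:

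- The control rate is "a 10% abandonment or reduction in the control group".
- The target is "identification of a difference equal to or greater than 8% between the intervention group and control group", which makes 18% in the intervention arm.
- The error rates are "an alpha risk of 0.05, and a beta risk of 0.20 in a two-tailed contrast".
- The size is to "randomize a total of 590 subjects (295 in each group").
- Losses are allowed for with the words "Taking into account a withdrawal rate of 10" per cent, which brings the total to 649.

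The Main outcome variables section requires abstinence to be validated by coximetry at 12 months.

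**The concern.** Where the success rate is low, assigning success to every lost control moves the comparison quickly. Each percentage point of loss adds almost a full point to the control rate and takes a little from the intervention rate. The planned effect is only 8 points, so a few per cent of losses can use it up.

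The article nevertheless tells the reader that the approach holds up to 20% losses, twice the loss that it plans for. A reader who trusts that limit could take an adverse worst-case result at 10% or 15% loss as evidence against the intervention, when it follows mechanically from the imputation. A check that turns adverse for a trial that met its target exactly also says little about whether a real result is fragile. No other missing-outcome analysis is stated to fill that gap.

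**Working it through.** **Reproducing the plan's figure.** Inputs are 10% and 18%, two-sided alpha 0.05 and power 80%. With pooled variance under the null and no continuity correction, n = [1.96 × sqrt(2 × 0.14 × 0.86) + 0.842 × sqrt(0.10 × 0.90 + 0.18 × 0.82)]² / 0.08² = about 294.1, so 295 per group and 590 in total. Then 590 × 1.10 = 649, or about 324.5 per arm. The rates used below are therefore the ones behind the plan's sample size.

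**Worst case as a function of loss.** Let L be the loss, equal in both arms, with the planned rates holding among those followed.

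- Intervention: 0.18(1 - L)
- Control: 0.10(1 - L) + L
- Difference: 0.08 - 1.08L

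The difference is zero at L = 0.08/1.08 = 7.4%.

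The test is z = difference / sqrt(2p(1 - p)/n), where p is the mean of the two rates, at expected counts. Confidence intervals use the unpooled standard error. With n = 324.5 per arm:

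| Loss | Intervention | Control | Difference (points) | 95% CI | p |
|---|---|---|---|---|---|
| 0% | 18.0% | 10.0% | +8.0 | +2.7 to +13.3 | 0.003 |
| 2% | 17.6% | 11.8% | +5.8 | +0.4 to +11.3 | 0.036 |
| 5% | 17.1% | 14.5% | +2.6 | -3.0 to +8.2 | 0.36 |
| 10% | 16.2% | 19.0% | -2.8 | -8.7 to +3.1 | 0.35 |
| 15% | 15.3% | 23.5% | -8.2 | -14.3 to -2.1 | 0.008 |
| 20% | 14.4% | 28.0% | -13.6 | -19.8 to -7.4 | below 0.001 (z = -4.24) |

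z falls to 1.96 at L of about 2.3% (2.1% with 295 per arm).

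**Effect needed to stay significant.** Against a 10% control rate with 324.5 per arm, the intervention rate among those followed would have to be about 28% at 10% loss (0.282 × 0.9 = 25.4% versus 19.0%, z = 1.96). At 20% loss it would have to be about 44% (0.439 × 0.8 = 35.2% versus 28.0%, z = 1.96). The plan targets 18%.

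**Other readings.**

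- Loss read as 59 of 649 (9.1%): 16.4% versus 18.2%, or -1.8 points.
- 10% and 18% read as rates among all randomised with losses already counted as failures: the difference is 0.08 - L, which is zero at 8% and -2.0 points at 10%.
- The Sample size calculation section gives its rates for abandonment or reduction, whereas the primary outcome is prolonged abstinence. With the 13.6% versus 6.4% that the Background cites from the lung-age trial, 10% loss gives 0.136 × 0.9 = 12.2% versus 0.064 × 0.9 + 0.10 = 15.8%, or -3.5 points.
- Unequal losses, 10% intervention and 5% control: 16.2% versus 14.5%, or +1.7 points (p = 0.57 with 295 per arm). There is no reversal, but no support for the effect either.

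**The case against.** The strongest defence is that a worst case is meant to be pessimistic. The article sets no pass mark: it says only that the size of the change from the initial results will be assessed. Nothing requires the worst case to stay significant or keep its sign, and it does not replace the main result. All of that stands. It does not rescue the 20% limit. As a bound, the calculation is valid at any loss rate, so a limit adds nothing. As an informative check, it has run out well before 20%.

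Three stronger readings are tempting, and the documents do not support them.

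- A reader might infer that the check must fail at the planned loss. That depends on an effect of exactly 8 points and equal losses, while the article plans for 8 points or more. With 25% versus 10% among those followed (an illustration), 10% loss gives 22.5% versus 19.0%. At 10% loss with the planned rates, the reversal is in the point estimate only.
- A reader might infer that the main result will rest on completers, because no rule is given for the initial results. The article may leave that rule to a fuller plan that is not shown. The intention-to-treat statement and the coximetry requirement both point the other way.
- A reader might take the exclusion criterion "Patient refusal to continue with the study" as removing people after randomisation. It is listed among the entry conditions. Consent comes at visit 0, and allocation follows only after spirometry, so refusal before allocation is the natural meaning. Losses are also to be counted within each group.

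**Conclusion.** The point holds in a limited form and is a should-fix. The 20% validity limit is unsupported by the plan's own figures: the worst-case comparison loses significance at about one tenth of that limit and changes sign at little more than a third of it. At the limit itself, it would show apparent significant harm in a trial whose planned benefit is fully present among those followed.

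These results assume the planned 10% and 18% among those followed, equal losses, and about 324 per arm. The alternative readings of the loss and of the rates shift the figures by a point or so and leave the conclusion unchanged. Unequal losses can avoid the reversal without making the check informative. The sample size is not in question here, and neither is the use of a worst case as an outer bound.

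**What to change.** 1. Delete the sentence on validity up to 20%.
2. State the main analysis: all randomised participants are in the denominator, and anyone without CO-confirmed abstinence at 12 months counts as not abstinent, in both arms. This follows from the coximetry requirement and the intention-to-treat statement.
3. Replace the single worst case with a tipping-point grid over arm-specific abstinence rates among the lost, keeping the worst case as its extreme corner. To illustrate at 10% loss, with every lost intervention participant smoking and a proportion q of lost controls abstinent, the difference is 0.162 - (0.09 + 0.10q). It stays significant with 324.5 per arm up to q of about 19% (16.2% versus 10.9%, z = 1.96) and changes sign at q = 0.072/0.10 = 72%. Readers can judge whether such rates are plausible, which the corner alone does not let them do.

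The cost is wording and one small table. Recruitment, visits and treatment do not change. Counting losses as not abstinent dilutes the difference somewhat: at 10% loss it is 0.18 × 0.9 = 16.2% versus 0.10 × 0.9 = 9.0%, or 7.2 points, with about 79% power at 324 per arm. It can also bias the estimate if losses differ between arms, and the grid would show this. The rule should be fixed before the analysts, who are blinded to group, learn the allocation.
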